### Concealment mechanism {16b}

The use of Stata to randomize using a password restricted website will ensure concealment.

### Implementation {16c}

Randomization was implemented by only one research assistant who is not involved in the trial in any way. Participants will be informed about their allocation via mail.

## Assignment of interventions: blinding

### Who will be blinded {17a}

This study is an open trial. Both patients and researchers know the group assignments in the trial and only the statisticians are blinded to the grouping.

### Procedure for unblinding if needed {17b}

No procedures are needed for unblinding until the finalization of the main data analysis.

## Data collection and management

### Plans for assessment and collection of outcomes {18a}

The time points of patient recruitment, intervention, data collection, processing, and follow-up operations are described in Table1. The collected data will be entered into the electronic data system of our reproductive medicine center.

### Plans to promote participant retention and complete follow-up {18b}

There is no additional incentive for participants to complete the trial. Based on our experience, participants are usually grateful for any research conducted due to the strong reproductive requirements.

### Data management {19}

All study staff, including outcome assessors and statisticians, will be well trained about data management. The collected data will be entered into the electronic case report form of our reproductive medicine center and stored on a secure server. The private information of patients (name, telephone number, and ID number) will be kept anonymous to ensure participant confidentiality. The clinical research associates are responsible for verifying the accuracy of the data and ensuring that the information will not be disclosed.

### Confidentiality {27}

Paper files will be kept in a locked filing cabinet in the treating hospital. Electronic documents will be stored in a password-protected computer, with access restricted to the principal investigator. All research documents will be preserved for at least 5 years after publication.

### Plans for collection, laboratory evaluation, and storage of biological specimens for genetic or molecular analysis in this trial/future use {33}

Not applicable—no identifying images or other personal or clinical details of participants are presented here or will be presented in reports of the trial results. Informed consent materials are available from the corresponding author on request.

## Statistical methods

### Statistical methods for primary and secondary outcomes {20a}

SPSS 13.0 software was used for analysis. The *χ*^2^ test will be applied to detect the differences in counting data (such as the clinical pregnancy rate, implantation rate, and abortion rate). Comparison of the measurement data (such as age, the basic FSH level, the AFC, Gn dosage and days, the number of eggs taken, and the fertilization rate) between groups will be performed using an independent sample *t* test. A *P* value < 0.05 will be considered statistically significant.

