**Enrollment:**						
Eligibility screen	X					
Informed consent	X					
Randomization	X					
Basic information login	X					
Physical examination	X					
Medical/treatment history	X					
Pelvic ultrasound		X			X	
Serum E2, P level		X				
**Intervention:** Embryo quality			X			

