### Sample size {14}

The sample size calculation is based on the clinical pregnancy rate. Retrospective data analysis (from January 2019 to December 2020, a total of 490 cycles of D6 single blastocyst transfer) showed that the clinical pregnancy rate of D6 single blastocyst transfer was approximately 49%. In our present study, we hope to improve the clinical pregnancy rate to 60%, the two-sided significance level will be set at *α* = 0.05, and the statistical power will be calculated as 1 − *β* = 0.90. The ratio between groups will be 1:1. The number of samples required for each group is 430. According to the 5% loss rate, there should be no fewer than 450 participants in each group, for a total of 900 participants.

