### Methods for additional analyses (e.g. subgroup analyses) {20b}

No additional analyses are planned.

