### Methods in analysis to handle protocol non-adherence and any statistical methods to handle missing data {20c}

Data will be analyzed following the ITT principle. Missing data will be analyzed. The imputation of missing values is not intended, although multiple imputations might be used within sensitivity analyses assuming data are missing at random.

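### The only analysis named for the primary outcome is an unadjusted chi-square; prespecified adjustment for age and previous transfers would be a small, nearly free gain in precision (minor)

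*Protocol article*

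**What the plan says.** The statistical methods section {20a} gives one method for rates: a chi-square "test will be applied to detect the differences in counting data", with the rates of clinical pregnancy, implantation and abortion as its examples. No covariate is named. The same section compares continuous characteristics between arms by t test, "such as age, the basic FSH level, the AFC" and four others, with significance at P < 0.05.

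Section {20b} says "No additional analyses are planned". Section {20c} adds the ITT principle and says that "multiple imputations might be used within sensitivity analyses assuming data are missing at random". Sequence generation {16a} specifies 1:1 allocation and mentions no stratification factor.

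The inclusion criteria {10} limit age to 20 to 38 years and require fewer than three transfer cycles. In Table 1, treatment history is taken at T1, the column that also holds randomisation. "Embryo quality" appears only at T3, the day of transfer.

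The sample size section {14} starts from "the clinical pregnancy rate of D6 single blastocyst transfer was approximately 49" percent and says "we hope to improve the clinical pregnancy rate to 60" percent, with two-sided alpha 0.05, power 0.90, 430 per group before loss and 450 after.

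**The concern.** Age and number of previous transfers must be known before a woman can be declared eligible, so they precede allocation even though Table 1 puts screening and randomisation in one column. If they carry prognostic information, a prespecified adjusted analysis estimates the same risk difference with a smaller standard error and accounts for chance imbalance. The article instead uses age only in a significance test between randomised arms. Under proper randomisation any such difference is chance, so the P value answers no useful question.

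Those tests also have a small practical cost. Seven variables are listed: age, FSH, AFC, gonadotrophin dose, gonadotrophin days, oocytes retrieved and fertilisation rate. If the tests were independent (an assumption), the chance of at least one P < 0.05 by luck is 1 − 0.95^7 = 30%. With no adjusted model prespecified, such a result invites adjustment chosen after seeing the data. What is at stake is a little precision and a cleaner answer to that situation, not the validity of the trial.

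**Working it through.** **1. The plan's own figure.** Inputs from section {14}: p0 = 0.49, p1 = 0.60, two-sided alpha 0.05, power 0.90, ratio 1:1. Mean proportion 0.545.

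n = [1.960·√(2·0.545·0.455) + 1.2816·√(0.49·0.51 + 0.60·0.40)]² / 0.11²
= [1.3803 + 0.8970]² / 0.0121 = 428.6, so 429 per group against 430 stated. It reproduces.

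**2. Power of the unadjusted test at 430 per arm.**

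- SE under the null = √(2·0.545·0.455/430) = 0.03396
- SE under the alternative = √(0.4899/430) = 0.03375
- Power = Φ[(0.11 − 1.960·0.03396)/0.03375] = Φ(1.287) = 90.1%

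**3. Is the unadjusted comparison biased?** A simulation used 4,000 trials per scenario, 430 per arm, with outcomes depending on age and previous transfers. The odds ratio, the same per 5 years of age and per previous transfer, ran from 1.0 to 0.6. Assumed: age about normal (31, SD 4) truncated to 20–38, and 0/1/2 previous transfers in 50/30/20% of women. In the four scenarios with prognostic covariates the mean unadjusted risk difference was 0.110 to 0.111 against a true 0.110. Type I error was 4.5 to 5.8% over all scenarios. There is no sign of bias.

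**4. What adjustment would gain.** None of the covariate effects is in the documents, so all are assumed. The age and transfer distributions are as in step 3, and good-grade blastocysts are assumed at 50%. Let m0 and m1 be a woman's pregnancy probabilities in each arm given her covariates, with intercepts set so that they average 0.49 and 0.60.

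- Unadjusted: n·Var = 0.49·0.51 + 0.60·0.40 = 0.4899
- Adjusted (standardised risk difference): n·Var = E[m0(1−m0)] + E[m1(1−m1)] + Var(m1−m0)/2
- Efficiency gain = 0.4899/(adjusted value) − 1. Power follows from step 2 with n = 430·(1 + gain).

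| Assumed OR: per year of age; per previous transfer; good vs poor grade | Age and transfers only: efficiency; power | Adding grade known before allocation: efficiency; power |
|---|---|---|
| 0.97; 0.90; 1.5 | +0.5%; +0.1 points | +1.5%; +0.4 points |
| 0.95; 0.85; 2.0 | +1.2%; +0.3 points | +4.1%; +1.1 points |
| 0.93; 0.80; 2.5 | +2.4%; +0.7 points | +7%; +1.9 points |

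**5. Cross-check.** In the step 3 simulation, unadjusted against adjusted power was 90.2 vs 90.1% (OR 0.9), 90.8 vs 90.8% (0.8), 90.5 vs 91.5% (0.7) and 89.8 vs 91.2% (0.6). Each figure has a Monte Carlo SE of about √(0.9·0.1/4000) = 0.5 points. An OR of 0.93 per year is 0.93^5 = 0.70 per 5 years, so the 0.7 row is the nearest match to the strongest case in step 4, with a somewhat stronger transfer effect. The two agree in order of magnitude.

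**The case against.** The strongest reply is that nothing here is wrong. A chi-square is a standard test for a 1:1 randomised binary outcome, it matches the sample size calculation, and it delivers the stated power. Covariate adjustment is often left to a statistical analysis plan, which is not shown. The documents nowhere state or quantify that age or transfer history predicts pregnancy in these women, and eligibility narrows both. All of this stands, and it is why the point is minor. What remains is that the article names one unadjusted method, plans nothing additional, and uses age only in a t test.

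Three stronger readings are tempting and not supported:

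- **That the unadjusted test gives up protection against bias.** Under randomisation the comparison is unbiased, and chance imbalance is already allowed for in its error rate. Adjustment would not repair the effects of an open label or of a denominator limited to women who received a transfer.
- **That staff who know the arm could choose the better blastocyst for one group.** Table 1 lists embryo quality at T3 and the trial is open, but the article does not say when the blastocyst is chosen or whether its grade is already on record. This is an inference about conduct, and an outcome model is not its remedy.
- **That all further analysis is ruled out.** Section {20c} allows multiple imputation in sensitivity analyses.

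**Conclusion.** The point holds as a minor improvement. The planned analysis is valid and adequately powered. Adjusting for age and previous transfers would add about 0.5 to 2.4% in efficiency, or 0.1 to 0.7 points of power at 430 per arm.

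A reader might infer a larger benefit by counting blastocyst grade. The range rises to about 1.5 to 7%, or 0.4 to 1.9 points, but only if a grade recorded before allocation exists, and the article lists embryo quality only on the day of transfer.

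These ranges rest entirely on the assumed odds ratios and covariate distributions. If the covariates predict nothing, the gain is nil. The stated sample size need not change either way.

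**What to change.** Before the statistician is unblinded, specify as the primary analysis a logistic model with arm, age (continuous) and number of previous transfers (0/1/2). Report the standardised risk difference with its 95% confidence interval. This keeps the effect on the scale on which the trial was sized, unlike a conditional odds ratio. Keep the chi-square as a sensitivity analysis, and amend section {20b} to agree.

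Replace the t tests between arms with descriptive summaries by arm.

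Add pre-freeze blastocyst grade to the model only if it is on record before allocation. Do not use the T3 grade, since it is recorded after allocation in an open trial.

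The cost is a few lines of analysis text and a short piece of code for the standardisation. Age and transfer history are already needed for eligibility, so no new data are required. The one condition is that the model is fixed in writing before unblinding.

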### Interim analyses {21b}

No interim analyses are planned.

### Methods for additional analyses (e.g. subgroup analyses) {20b}

No additional analyses are planned.

### Methods in analysis to handle protocol non-adherence and any statistical methods to handle missing data {20c}

Data will be analyzed following the ITT principle. Missing data will be analyzed. The imputation of missing values is not intended, although multiple imputations might be used within sensitivity analyses assuming data are missing at random.

### Plans to give access to the full protocol, participant level-data and statistical code {31c}

There is no additional protocol to this version. Any data, statistical code, or documentation may be provided by the corresponding author upon request.

## Oversight and monitoring

### Composition of the coordinating center and trial steering committee {5d}

Since this is a single-center trial, a formal coordinating center is not deemed necessary. The study team meets weekly. Principal investigators will join the meeting monthly.

### Composition of the data monitoring committee, its role and reporting structure {21a}

Given the small size of our monocentric trial with few researchers involved and without funding, there is no need for an additional data monitoring committee.

### Adverse event reporting and harms {22}

Adverse events (AEs) are defined as any untoward or unfavorable medical occurrences associated with the subject’s participation during the research. AEs in this study will be divided into study-related AEs and non-study-related AEs, which will be judged by clinicians at the time of recording. AEs related to the study will include hepatic injury and thrombosis. AEs related to Femoston and progesterone include nausea, dizziness and headache, fatigue, measles, breast swelling, menorrhagia or amenorrhea, hepatic dysfunction, edema, and weight gain.

All AEs will be recorded in detail. Once any adverse reaction occurs during medication use, the drug will be stopped immediately. Serious AEs will be reported to the principal investigator immediately, and appropriate measures will be initiated instantly. The ethics committee will determine whether the AE is likely to have been associated with the experimental drug and whether it is necessary to break the blinding codes.

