#### Endometrial preparation

All the included patients will undergo an HRT cycle for endometrial preparation. Treatment will start on day 2 or day 3 of menstruation with oral Femoston (estradiol 2 mg po tid). After approximately 10–12 days of estrogen treatment, a transvaginal ultrasound will be performed to measure the endometrial thickness. Two procedures for further treatment depending upon the endometrial thickness are listed as follows:If the endometrium thickness is not less than 8 mm, patients will continue to take Femoston (estradiol tablet). On days 16–20 of the HRT cycle, patients will be changed over to receive oral Femoston (2 mg estradiol and 10 mg dydrogesterone tablet, po tid) and intramuscular injections of progesterone (60 mg qd) to transfer the endometrium into the secretory phase.If the endometrium thickness is less than 8 mm, the dose of oral Femoston (estradiol tablet) will increase to 8 mg until the endometrium thickness reaches 8 mm. On days 18–20 of the HRT cycle, Femoston (2 mg estradiol and 10 mg dydrogesterone tablet, po tid) and progesterone (60 mg qd) will be administered to transfer the endometrium into the secretory phase. If the endometrium thickness is still less than 8 mm, it should be discussed with patients whether to proceed with FET or abandon the protocol.

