#### Corpus luteum support

Estradiol valerate will be stopped gradually after 8 weeks of FET; vaginal progesterone gel or oral dydrogesterone will be continued for 8 weeks of FET.

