### Outcomes {12}

#### Primary outcome measure

The primary outcome measure is the clinical pregnancy rate: the ratio of the clinical pregnancy (intrauterine gestation sac with a fetal heart beat) number to the number of patients who received embryo transfer.

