### Participant timeline {13}

The participant timeline is shown in Table1.

**Table 1 Tab1:** SPIRIT figure: schedule of enrollment, interventions, and assessments

Timepoint	Study period					
	Enrollment			Post-allocation		
	T1	T2	T3	T4	T5	T6
	Day of progesterone supplementation	Period of HRT-cycle	Day of embryo transfer	14 days after transfer	30/42 days after transfer	After delivery

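### The adverse event section stops the drug for any reaction, however mild, and the withdrawal criteria end follow-up for women whom ITT must count

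*Protocol article*

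**What the plan says.** **Stopping rule.** Adverse event reporting and harms {22} states: "Once any adverse reaction occurs during medication use, the drug will be stopped immediately". Among the events it attributes to Femoston and progesterone are "nausea, dizziness and headache, fatigue, measles, breast swelling". Seriousness appears only in a separate instruction on reporting and measures: "Serious AEs will be reported to the principal investigator immediately". The section on access to the full protocol {31c} adds: "There is no additional protocol to this version".

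**Regimen.** Before transfer, Endometrial preparation gives estradiol first, then "oral Femoston (2 mg estradiol and 10 mg dydrogesterone tablet, po tid) and intramuscular injections of progesterone (60 mg qd". After transfer, Corpus luteum support names estradiol valerate, tapered after 8 weeks, and separately says that "vaginal progesterone gel or oral dydrogesterone will be continued for 8 weeks of FET". The ultrasound for the primary outcome is 30 days after transfer (Follow-up evaluation).

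**Timing and denominator.** Table 1 (Participant timeline {13}) puts randomisation at T1, labelled "Day of progesterone supplementation". It schedules adverse event assessment at T2 and T3 only, so not after the day of transfer. The primary outcome is the ratio of the clinical pregnancy "number to the number of patients who received embryo transfer".

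**Follow-up.** The Withdrawal criteria under {11b} class women who do not comply with treatment, or who unexpectedly withdraw from transfer, as unsuitable for continued follow-up. The Suspension criteria include treatment-related adverse events, again with no severity limit. Section {20c} promises analysis by ITT.

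**The concern.** In an HRT cycle the hormones prepare the endometrium, and the trial compares two days of progesterone exposure on which to transfer. A rule that withdraws a hormone for nausea or fatigue therefore acts on the regimen under study. If staff obey it, women leave the planned regimen for reasons that need no such step. If staff use sensible judgement instead, each mild symptom that is managed without stopping becomes a departure from the protocol.

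The second matter is separate and does not depend on the stopping rule. ITT requires the outcome of every randomised woman. Criteria that end follow-up for non-compliance or a withdrawn transfer lose exactly the outcomes that ITT needs.

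**Working it through.** **1. Is the stopping rule limited anywhere?** The trigger is any adverse reaction during medication use. Mild symptoms are named as drug-related in the same section. Serious events have their own sentence, which concerns reporting and measures and is not a condition for stopping. No section gives a grade, dose reduction, substitution or restart rule, and {31c} rules out a fuller protocol. The rule is stated, and it is broad.

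**2. When can it act after randomisation?**
- Between T1 (start of progesterone) and transfer on the 6th or 7th progesterone day, so about a week. Symptoms on estradiol alone, before T1, cannot cause a loss after randomisation.
- After transfer, during the 8 weeks of support, which include the 30-day ultrasound.

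**3. What would a stop remove?**
- Before transfer, Femoston is by then a combined estradiol and dydrogesterone tablet. Stopping it removes both unless estradiol is replaced. An estradiol-only tablet is in use earlier in the same cycle, so a replacement exists, but none is ordered. Intramuscular progesterone is a separate product.
- After transfer, estradiol valerate is listed apart from the progestogens. A progestogen stop need not end estradiol, and two progestogen options are named.

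**4. The plan's sample size.** Inputs from Sample size {14}: 49% v 60%, two-sided alpha 0.05, power 0.90, 1:1 allocation.

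n per arm = [1.960 × √(2 × 0.545 × 0.455) + 1.282 × √(0.49 × 0.51 + 0.60 × 0.40)]² / 0.11²
= [1.960 × 0.7042 + 1.282 × 0.6999]² / 0.0121 = 428.6, so 429.

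The stated 430 reproduces.

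Power = Φ{[difference × √n − 1.960 × √(2p̄(1 − p̄))] / √(p₁(1 − p₁) + p₂(1 − p₂))}, where p̄ is the mean of p₁ and p₂. This gives 90.1% at 430 per arm and 91.3% at the 450 per arm to be enrolled.

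**5. Illustration of size.** The documents give no stopping rate and no loss after stopping. Every x and l below is an assumption, taken as equal in both arms.

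(a) A share x is dropped from the analysis, rates unchanged:

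| x | n per arm | Power |
|---|---|---|
| 5% | 428 | 90.0% |
| 10% | 405 | 88.3% |
| 20% | 360 | 84.4% |

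The 5% row is the loss that the sample size section already allows for.

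(b) All 450 per arm are counted. A share x stops after transfer and a share l of their pregnancies is lost, so both rates are multiplied by (1 − x × l):

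| x | l = 25% | l = 50% | l = 100% |
|---|---|---|---|
| 5% | 90.6% | 89.8% | 88.2% |
| 10% | 89.8% | 88.2% | 84.5% |
| 20% | 88.2% | 84.5% | 76.0% |

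(c) A share x stops before transfer, transfer is cancelled, and the women are counted as not pregnant. This is the l = 100% column. The 11-point difference shrinks to 11 × (1 − x) = 10.45, 9.9 or 8.8 points.

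With x = 2% and total loss, power is still 90.1%.

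**6. Follow-up against ITT.** The Withdrawal criteria remove non-compliant women and those who withdraw from transfer, whereas {20c} analyses by ITT. The two cannot both be carried out. Whether a woman stopped or suspended for an adverse event also leaves follow-up is not stated.

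**The case against.** The strongest reply is that the sentence is generic safety wording. The same section speaks of an experimental drug and of blinding codes, yet the trial is open and both arms receive the same hormones. The drug is thus undefined, and stopping one product need not end support. Stopping on a suspected reaction is cautious and applies to both arms alike. No section says that a reaction cancels a transfer, and after transfer no adverse event assessment is scheduled that would trigger the rule.

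Most of this stands, and it limits the point. A reader might infer that a mild symptom ends all hormone support after transfer, estradiol included. Corpus luteum support does not bear that out, because estradiol is a separate product there. A reader might also infer that the rule costs the trial its power or biases the comparison. The documents do not show that either: the 76.0% figure needs one woman in five to stop with every pregnancy lost, and no difference in stopping between arms is shown.

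It is also fair that loss from the denominator and from follow-up arises from the outcome definition and the Withdrawal criteria. Both would remain if the stopping rule were corrected.

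The reply does not supply a severity threshold. The sentence still orders a stop for any reaction, and an undefined drug makes the instruction less clear, not narrower.

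**Conclusion.** The point holds as a modest correction to two pieces of wording. First, the stopping rule has no severity limit and, read literally, takes women with mild symptoms off the planned regimen before or after transfer. Second, and independently, the Withdrawal criteria conflict with ITT.

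The size is unknown and probably small. Under the assumed rates, power stays at or above 88.2% when 5% stop, even if all their pregnancies are lost. These figures rest on assumed stopping and loss rates, equal in both arms, and on the plan's 49% and 60%. They do not demonstrate lost power or bias. The change is worth making because it is cheap and spares women an avoidable break in treatment.

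**What to change.** **Adverse event reporting and harms {22}.** Limit the immediate stop to serious or clinically significant treatment-related reactions, in both arms alike. Otherwise continue treatment, or substitute: a progestogen named under Corpus luteum support, and estradiol-only tablets if the combined Femoston tablet is stopped before transfer.

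**Withdrawal and Suspension criteria {11b}.** State that stopping treatment, a cancelled transfer or suspension does not end follow-up unless the woman withdraws consent, and that her pregnancy outcome is counted in her randomised arm. This brings the criteria into line with {20c}.

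**Cost.** A wording amendment with ethics committee approval, as the amendments section {25} requires, and no added visits or patients. The downside is that some women with mild symptoms stay on treatment.
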